### The intervention

In the pharmacy, the pharmacist will intervene at the second dispensing for those patients with a PROMAS score that signals an increased nonadherence risk. In the intervention pharmacies, the barrier profile (see Fig. 2), in combination with the manual, will be used as a systematic decision support tool to tailor interventions to the identified cognitive, emotional, and practical adherence barriers. The manual serves as a guideline for discussing the identified barriers and determining an intervention to address them. Table 2 describes two examples of barriers with recommendations from the manual on how to address these barriers and to choose an intervention. In the barrier profile, the extent to which each of the eight potential barriers are present will be depicted graphically in three gradations (see Fig. 2).

**Fig. 2 Fig2:**
[figure not shown]
Example of a barrier profile. The profile shows eight potential adherence barriers: two emotional barriers (feelings with regard to medication and fear of side effects); one emotional/cognitive barrier (concerns about medication usage); two cognitive barriers (necessity beliefs and attitude with regard to medication); one cognitive/practical barrier (self-efficacy), and two practical barriers (inconvenience and knowledge about medication scheme)

**Table 2 Tab2:** Examples of recommendations on how to address the barriers in an intervention

*■* In case “fear of side effects” seems to be a barrier
○ Ask questions to try to find the cause(s) for de fear of side effects and identify the influence of external factors such as media and other persons.
○ Focus on the elimination of the fear, using the following possibilities:
- explain that the medication can cause side effects and provide the patient information about the “number needed to harm,
- discuss the balance between the risk for side effects and the desired effect,
- discuss the best way for medication intake to prevent side effects, and
- agree about the intake of the medication and encourage the patient to report existing side effects.
Examples of questions:
○ How do you generally think about the fact that you need to take medication?
○ What is your attitude toward medication, and toward the prescribed medication in particular?
○ What information did you get about the benefits of the medication?
○ For which side effects do you have fear and where does it come from?
○ Did this fear always exist or did it change? What caused this change?
○ How does this fear influence you? What is the effect on your medication intake?
○ Do you have information on your risk for particular side effects? ○ Which side effects play a major role in your well-considered decision on the intake of this medication?
○ Which side effects do you expect, and to what extent do they prevent you from medication intake?
○ Let’s go through the information leaflet to discover which side effects can possibly occur in your case.
*■* In case “knowledge about medication scheme” seems to be a barrier:
○ Discuss the prescribed use of the new medication.
○ Discuss the use of other chronic medication and assimilate the new medication into the patient’s medication scheme.
○ Take the patient’s customs into account.
○ Explain the importance of regular medication intake for the efficacy of the medication and the possible side effects and interaction with other medication.
○ Choose the most appropriate option for the patient:
- consider whether medication synchronization or a repeat prescription service will be helpful for the patient,
- consider reminders for medication intake,
- consider the use of a pill box at the start of each week with all medications,
- consider streamlining medication regimens and the development of a new treatment plan, and
- consider to involve an informal caregiver.
Examples of questions:
○ Do you have sufficient knowledge about your new medication scheme including all your medication?
○ Is this medication scheme feasible for you?
○ Do you need any support with regard to your medication intake?

All interventions start with a discussion of the barrier profile with the patient in a manner that makes use of the patient-centered techniques. When cognitive or emotional barriers (e.g., attitude with regard to medication, concerns about medication usage, and fear of side effects) are present for the specific patient, the pharmacist starts to discuss the relevant issues in the profile using the recommendations of the manual and the patient-centered communication techniques to try to take away or diminish these barriers. The manual proposes the following main intervention strategies: for patients with an insufficient awareness of the need to use the medication, self-assessment of clinical measures (blood pressure and blood glucose) will be proposed, since this has been shown to increase medication adherence. When agreed on by the patient, this will be initiated in the pharmacy by providing the patient the relevant devices. When barriers mainly appear to be practical for the specific patient (inconvenience and/or knowledge about medication scheme), the pharmacist offers one or several practical solutions, e.g., suggestion for medication change, pill organizer, use of a Baxter system, reminders, seek the help of the patient’s social network, or simplification of dosage scheme. The pharmacist registers the intervention.

Since the pharmacist as well as the GP and the nurse practitioner are involved in supporting their patient with their medication use, a good communication and cooperation among all these parties is needed.

Technology-based systems that enable easy communication between healthcare providers about the progress of interventions and agreement about allocation of time and resources are required for optimal functioning of the medication-adherence tool. The chain information system Care2U is the preferred way to communicate all information about the interventions. Currently, the system needs some adaptations in order to enable such communication between pharmacy and general practice. In case such communication is not possible by the time of the start of the study, other ways of communication (telephone, email, or fax) between pharmacists and GPs will be agreed upon.

### Implementation of the medication-adherence tool

To deliver the tailored intervention, training on a patient-centered communication technique will be offered to the pharmacists, and one of the pharmacy assistants of the pharmacies assigned to the intervention group. Intervention pharmacists and their pharmacy assistants will receive a three-hour training session before starting the trial, consisting of a brief introduction to the proposed communication technique, demonstration of a second dispense moment with a barrier profile, and skills practice using role play. The pharmacists and pharmacy assistants will be specifically instructed on discussing the profile with the patients in order to offer a tailored intervention to overcome cognitive, emotional, or practical barriers.

Intervention pharmacies will also receive a manual containing instructions for discussing and overcoming the various potential barriers for medication adherence. In this manual, potential barriers are categorized into cognitive, emotional and practical nonadherence barriers. Furthermore, intervention pharmacies will receive a follow-up group session from the trainer on the patient-centered communication technique to provide support and exchange experiences on discussing the barrier profiles. In addition, three members of the research team will visit all participating pharmacists. At least the pharmacist and one experienced pharmacy assistant of a pharmacy will be present during that appointment. We will explain the study in detail and provide them with an easy-to-understand explanation of the workflow concept and subsequently discuss how the workflow concept can be optimally tailored to existing routine work procedures in the pharmacy. One of the researchers will be available during working hours to answer questions arising from the study. Finally, pharmacists will be offered the opportunity to contact one of the pilot pharmacists to ask questions and advices about the study procedures. Table 3 summarizes the various elements of the implementation strategy.

**Table 3 Tab3:** Elements of the implementation strategy

*■* Visit of the pharmacy by the research team to provide the manual and to tailor the workflow concept to existing work procedures in an optimal way
*■* Training session for pharmacists on patient-centered communication, using the manual and discussing the barrier profile
*■* Follow-up group session of the trainer on discussing the barrier profile
*■* Onsite support on the use of the tablet
*■* Availability of researcher for answering questions about the study
*■* Possibility to contact pilot pharmacist for questions and advice on study procedures

### Measures

#### ProMAS

The Probabilistic Medication Adherence Scale (ProMAS) is an 18-item validated questionnaire to assess nonadherence behavior in general [12]. For the purpose of this study, the questionnaire will be slightly adapted for use with patients who do not take any other chronic medication and who have a first prescription of cardiovascular or oral blood glucose-lowering medication. The cut-off value for being at risk for nonadherence is 13: patients with a score of ≥ 13 are considered to have an increased risk for nonadherence, whereas patients with a score below 13 are not at risk for nonadherence. The ProMAS will be applied at baseline and at 8 months follow-up.

#### Scale on underlying barriers related to nonadherence

This questionnaire measures to what extent the following emotional, and practical barriers for nonadherence are present: feelings with regard to medication, fear of side effects, concerns about medication usage, necessity beliefs, attitude with regard to medication, self-efficacy, inconvenience, and knowledge about medication scheme.

#### Adherence

Medication adherence is calculated as the percentage of days covered by medication (PDC) based on pharmacy dispensing of one drug group since the start of the therapy until the end of the study period. Patients with a PDC of at least 80 % are labeled as “sufficiently adherent.” PDCs are calculated per medication group (see Appendix), except for blood glucose lowering drugs. As for diabetes, often, more than one drug is used, and patients have to adhere to each drug from the subclass, e.g. to biguanides and sulfanilamide derivatives. Data on dispensing will be based on routine pharmacy data collection.

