A measurement period of at least 8 months is preferred in order to get valid information from dispensing data. A first prescription is usually dispensed for 14 days, followed by a prescription for 90 days. After 8 months, at least two repeat prescriptions after the second dispensing must have had occurred to meet a PDC of 100 %. As we assume a PDC of 80 % is sufficient, at least (14 days + 180 days =) 196 days * 1.2 = 234 days = 7.8 months are needed to detect nonadherence. If the last patient was included after 14 months, together with the measurement period, this ends up the total study period with 22 months needed for follow up.

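### The primary PDC makes no allowance for a replaced drug, although the intervention can prompt a replacement, so misclassification may differ between the arms

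*Protocol article*

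**What the plan says.** In the protocol article, the Adherence section (under Measures) computes PDC "based on pharmacy dispensing of one drug group since the start of the therapy until the end of the study period", and adds: "PDCs are calculated per medication group (see Appendix), except for blood glucose lowering drugs". For glucose-lowering drugs the reason given is that several are often used together, and the rule is that "patients have to adhere to each drug from the subclass, e.g. to biguanides and sulfanilamide derivatives". A PDC of 80% or more counts as sufficient adherence. The Appendix lists diuretics (C03), beta-blockers (C07), calcium channel blockers (C08) and renin-angiotensin agents (C09) as separate groups.

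The section on the intervention says that "the pharmacist will intervene at the second dispensing for those patients with a PROMAS score that signals an increased nonadherence risk". When barriers are mainly practical, "the pharmacist offers one or several practical solutions, e.g., suggestion for medication change, pill organizer, use of a Baxter system, reminders", and the list goes on to a simpler dosing scheme.

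Under Outcomes, the primary comparison is restricted to patients at high initial risk and made at 8 months. Under Data analysis, PDC is compared both dichotomised at 80% and as a mean. The article does not say how a switch, a substitution or a prescriber's decision to stop is handled.

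**The concern.** The numerator counts supply of one group, while the denominator runs to the end of follow-up. A patient moved from a C07 drug to a C09 drug for the same purpose therefore collects uncovered days from the switch, even with perfect use of the new drug. Where each glucose-lowering agent must be adhered to, replacing one by another can fail the patient on the agent that was stopped.

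All PDC definitions have some noise of this kind. Here it matters more, because a change of medication is one of the options the tool offers, at the second dispensing, to the patients on whom the primary outcome is measured. A patient who follows the tool's advice could be scored as a failure. If such replacements are not equally frequent in the two arms, the primary contrast is distorted as well as diluted.

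**Working it through.** **Inputs from the Sample size section.** Control 60% nonadherent, so 40% adherent; effect 20 points, so 60% in the intervention arm; ICC 0.05; 14 pharmacies; 39 patients per pharmacy; power 80%; alpha 5%. Assumed: two-sided test, 7 pharmacies per arm, 8 months taken as 240 days.

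**Reproducing the plan.** With unpooled variance, n per arm = (1.960 + 0.842)² × (0.40×0.60 + 0.60×0.40) / 0.20² = 94.19. With 7 clusters per arm, m = n(1 − ICC)/(7 − n×ICC) = 94.19×0.95/(7 − 4.71) = 39.06, which agrees with the stated 39. Conversely, the design effect is 1 + 38×0.05 = 2.9, the effective size is 7×39/2.9 = 94.14 per arm, and power is 79.98%.

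**One patient.** The Sample size section states: "A first prescription is usually dispensed for 14 days, followed by a prescription for 90 days". For a patient who uses every drug perfectly but changes group:
- switch at day 14: PDC = 14/240 = 5.8%
- switch after the first 90-day refill, day 104: PDC = 104/240 = 43%
- switch at day 192 or later: PDC ≥ 192/240 = 80%, so still counted as adherent

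**The trial.** Let s0 (control) and s1 (intervention) be the share of otherwise adherent patients who switch across groups early enough to fall below 80%. The documents give neither share. Observed adherence is then 0.40(1 − s0) and 0.60(1 − s1), and power = Φ(difference / √[(p0(1 − p0) + p1(1 − p1))/94.14] − 1.96).

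| s0 control | s1 intervention | Observed | Difference | Power |
|---|---|---|---|---|
| 0% | 0% | 40% v 60% | 20 points | 80% |
| 0% | 5% | 40% v 57% | 17 points | 66% |
| 5% | 5% | 38% v 57% | 19 points | 76% |
| 10% | 10% | 36% v 54% | 18 points | 71% |
| 5% | 10% | 38% v 54% | 16 points | 61% |
| 10% | 5% | 36% v 57% | 21 points | 84% |

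**Direction.** The difference equals 0.20 − 0.60×s1 + 0.40×s0. It is below 20 points whenever s1 exceeds two thirds of s0, and above 20 points otherwise. Equal switching therefore already dilutes the contrast, and the error favours the tool only if intervention switching is less than two thirds of control switching.

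**Mean PDC** is affected too: a perfect user who switches at day 14 loses (240 − 14)/240 = 94 percentage points.

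**The case against.** The strongest reply is that the article is silent on switches, which is different from stating a wrong rule. It speaks of PDCs in the plural, so a new group might get its own PDC, and a full protocol or analysis plan could settle the combination. The reason given for the glucose-lowering rule is concurrent use, not replacement. This has some force, but the article does fix both the single group and the window to the end of the study, and nothing in it credits a replacement.

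A reader might infer that every switch is penalised, that only the intervention arm is affected, or that a bias against the tool is established. The documents support none of these:
- The groups are broad, so outside diabetes a change of agent within a group costs nothing, and a late switch is harmless.
- Medication change is one example among several, and nothing says that it crosses a group. A simpler dosing scheme need not cross one either.
- Control patients can also switch; the Study design section says that treatment after two weeks depends on the patient's experience.
- The manual's work on fear of side effects could reduce switching in the intervention arm.

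The 40% control rate may also already contain some switching, in which case reducing it again counts switching twice.

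Finally, a natural remedy would be to pool all drugs for one indication. That objection stands in full: eligibility is per drug class, so a patient already taking one antihypertensive class can enter on starting another, and supply of the older drug would hide abandonment of the started one.

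**Conclusion.** The point holds in limited form. As written, the primary PDC scores an early replacement by a drug from another group, or by another glucose-lowering agent, as nonadherence. The intervention may itself prompt such a replacement in the primary population, so the Adherence and intervention sections must be reconciled.

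The primary outcome is therefore open to misclassification that may differ by arm. The direction is probably against the tool, because medication change is a named component of the intervention and equal switching already shrinks the difference. It is not certain, and the article does not show it. The size is unknown. The tabulated range, from 16 to 21 points and 61% to 84% power, illustrates assumed rates and is not an estimate. It rests on switchers being otherwise as adherent as the rest of their arm, on early cross-group switches, and on the plan's 40% and 60% being free of switching. The stated 39 patients per pharmacy is not in question.

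**What to change.** Keep the per-group PDC for the started drug, and add a replacement rule to the Adherence section:
- A replacement is recognised when a study-group drug not in use at baseline is first dispensed and the started drug is not dispensed again afterwards.
- From that date, either credit the replacement's covered days or close the started drug's window. Choose one in advance. With a closed window, a day-14 switch is judged on the first supply alone, whereas crediting keeps the full follow-up.
- Apply the same rule when one glucose-lowering agent replaces another.
- Never count drugs already in use at baseline.
- Fix the rule before outcome data are seen, and report the literal per-group PDC as a sensitivity analysis.

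Reporting the number of replacements by arm would show whether the issue mattered.

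The cost is a few sentences and some programming on the same dispensing data. The downside is that a patient who is given an additional drug and then abandons the first will sometimes be read as having had a replacement, and so be judged too leniently. The sensitivity analysis shows how much depends on this.

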### Outcomes

The primary outcomes are as follows:The primary outcome is the difference in the medication adherence of patients with an initial high risk of nonadherence between the intervention and the control group, measured by pharmacy dispensing records at 8 months follow-up.

The secondary outcomes are as follows:Based on data from all patients participating:The difference in the percentage of patients with an increased risk for nonadherence based on the ProMAS between the intervention and control group at 8 months follow-upThe difference in percentage of patients with an increased risk for nonadherence based on the barrier profile between the intervention and control group at 8 months follow-upThe positive and negative predictive values of the ProMAS score and the barrier profile measured at drug initiation in the control group in relation to medication adherence at 8 months follow-upDifference in medication adherence in the subgroup of patients with a follow-up period of at least 1 year after drug initiation. This in fact means to assess an effect after a longer follow-up period of at least a year analogous to the primary outcome.

The process evaluation will address the following:The barriers and facilitators in the implementation of the use of the medication-adherence tool.

These influencing factors will be discussed with all pharmacists in the intervention arm by semistructured interviews. The assessment on barriers and facilitators will be based on the Tailored Implementation for Chronic Diseases’ (TICD) checklist. This is a comprehensive, integrated checklist with 57 potential determinants of practice grouped in seven domains: guideline factors, individual health professional factors; patient factors; professional interactions; incentives and resources; capacity for organizational change; and social, political, and legal factors [14].

Patients will also be interviewed about their experiences with the medication adherence assessment and interventions. Informed consent for these interviews will be obtained. Interviews will aim at gaining a better understanding of how patients and healthcare providers have experienced the intervention in terms of effort, time investment, and benefits. The purposive patient sample size will be determined based on theoretical saturation (data collection until no new information is obtained). Therefore, data review and analysis will be done in conjunction with data collection.

### Sample size

For the sample size calculation, the following assumptions are made: we assume that a percentage of 60 % is nonadherent in our sample of patients at high risk based on their ProMAS score. This assumption is reasonable according to published studies [6]. We assume that the intervention will increase the 80 % PDC in the intervention group by 20 % compared to the control group. As patients are clustered within pharmacies, the evaluation will be performed by multilevel analysis to adjust for clustering. For the effect of clustering, an intracluster correlation (ICC) of 0.05 was assumed.

In agreement with conventional power calculations, a power of 80 % to detect a true difference and a chance of 5 % of a type 1 error to wrongly conclude on a difference are assumed. For this trial, in the DOH/CAZO setting, we assume that there are at least 14 community pharmacies willing to participate. The sample size calculation results in 39 patients needed per pharmacy. PASS software version 11 was used to determine the appropriate sample size. Considering 30 % lost to follow-up during the study period, 56 patients need to be included per pharmacy to achieve the power needed. If only 50 % of the patients agree to join the study, 112 patients need to be invited per pharmacy.

In the potentially participating 25 pharmacies, a total of at least 6,081 single patients with primary dispensings of cardiovascular or oral blood glucose-lowering medications were detected within 12 months (as observed in historical data). This means that, on average, 20 subjects started with cardiovascular or oral blood glucose-lowering medication monthly per pharmacy. Assuming 40 % of the starters at risk for nonadherence (determined by a ProMAS score ≥ 13), this means, on average, that eight patients are available monthly per pharmacy for an intervention. The period to have 112 starters on cardiovascular or blood glucose-lowering medication per pharmacy will be approximately 14 months.

A measurement period of at least 8 months is preferred in order to get valid information from dispensing data. A first prescription is usually dispensed for 14 days, followed by a prescription for 90 days. After 8 months, at least two repeat prescriptions after the second dispensing must have had occurred to meet a PDC of 100 %. As we assume a PDC of 80 % is sufficient, at least (14 days + 180 days =) 196 days * 1.2 = 234 days = 7.8 months are needed to detect nonadherence. If the last patient was included after 14 months, together with the measurement period, this ends up the total study period with 22 months needed for follow up.

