##### Exclusion criteria

Patients will be excluded if they have any cognitive impairments or insufficient Dutch language skills as determined by the pharmacists' judgment. Inclusion numbers will be monitored; inclusion will be stopped when the targeted number is reached.

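### The per-pharmacy targets of 56 included and 112 invited are counts of high-risk patients, but the trial invites and includes all starters and the text calls the 112 starters

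*Protocol article*

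**What the plan says.** All places are in the protocol article.

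- **Population of the calculation (Sample size).** The control rate is set for high-risk patients: "we assume that a percentage of 60 % is nonadherent in our sample of patients at high risk based on their ProMAS score". The effect is that "the intervention will increase the 80 % PDC in the intervention group by 20 % compared to the control group". For clustering, "an intracluster correlation (ICC) of 0.05 was assumed", and for the number of clusters, "we assume that there are at least 14 community pharmacies willing to participate". The result is 39 patients per pharmacy.
- **Targets (Sample size).** After 30% loss to follow-up, "56 patients need to be included per pharmacy to achieve the power needed". With 50% participation, 112 must be invited.
- **Recruitment rate (Sample size).** Historical data give 20 starters a month per pharmacy. With 40% of them at risk, "eight patients are available monthly per pharmacy for an intervention". The section then concludes: "The period to have 112 starters on cardiovascular or blood glucose-lowering medication per pharmacy will be approximately 14 months".
- **Who is invited and included (Inclusion criteria; Outline of the study procedure for patients).** Eligibility has no risk criterion. Patients are invited at the first dispensing and complete the questionnaire later, as part of joining the study.
- **Stopping of inclusion (Exclusion criteria).** Numbers are monitored and "inclusion will be stopped when the targeted number is reached". That number is not defined there.
- **Primary outcome (Outcomes).** It is assessed in patients with an initial high risk only.

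**The concern.** The targets are calculated for one population and have to be applied to another. Nobody can invite or include 56 high-risk patients selectively, because risk is unknown until the patient has taken part in the baseline assessment. A recruitment target must therefore be expressed in starters, or recruitment must be counted by the baseline ProMAS result. The section does neither, and its last statement on recruitment attaches the high-risk figure of 112 to starters.

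This matters because inclusion ends at a target number. Someone monitoring recruitment could take 56 included or 112 invited starters per pharmacy as that number. Only about 40% of those patients would count towards the primary comparison.

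A lesser question is how firm the 80% power is, given that it rests on 14 clusters and that pharmacies are stratified as small or large.

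**Working it through.** **Inputs from the Sample size section:** adherent proportion 0.40 in controls (60% nonadherent) and 0.60 with the intervention; ICC 0.05; power 80%; type 1 error 5%; at least 14 pharmacies; 30% loss; 50% participation; 40% of starters at high risk; 6,081 starters in 25 pharmacies over 12 months.

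**Assumptions:** a two-sided test, 7 pharmacies per arm, and the 20% read as percentage points. The stated 39 supports these: they reproduce it, whereas a relative 20% increase (0.40 to 0.48) gives only about 20% power at 39 per pharmacy. The 40% high-risk share and the 30% loss are taken to apply equally to everyone included.

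**1. The plan's own figure**
- Effective number per arm: (1.96 + 0.8416)² × (0.24 + 0.24) / 0.20² = 94.2.
- Design effect at m = 39: 1 + 38 × 0.05 = 2.90.
- Effective number available: 7 × 39 / 2.90 = 94.1, so power is 80.0% by the normal approximation. The 39 reproduces.
- 39 / 0.70 = 55.7, rounded to 56; 56 / 0.50 = 112. Since 39 is a high-risk count, so are 56 and 112.

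**2. The recruitment period**
- 6,081 / 25 / 12 = 20.3 starters a month, of whom 20 × 0.40 = 8 are high risk.
- 112 / 8 = 14 months, as stated.
- 112 / 20 = 5.6 months if the 112 are starters, as worded.

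**3. The equivalent in starters**
- Included: 56 / 0.40 = 140 per pharmacy.
- Invited: 112 / 0.40 = 280 per pharmacy.
- Time: 280 / 20 = 14 months.
- Check: 280 × 0.50 = 140 included; × 0.40 = 56 high risk; × 0.70 = 39 analysed.

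**4. If recruitment stopped at 56 included (or 112 invited) starters per pharmacy**
- Analysable high-risk patients: 56 × 0.40 × 0.70 = 15.7 per pharmacy.
- Design effect: 1 + (15.68 − 1) × 0.05 = 1.734. Effective number per arm: 7 × 15.68 / 1.734 = 63.3.
- Normal approximation: 0.20 / √(0.48 / 63.3) − 1.96 = 0.34, so power is 63%. A non-central t with 12 df gives 56%.
- With all 25 pharmacies (12.5 per arm on average): 87% (normal) or 84% (t).

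**5. Secondary check: power at the full 39 high-risk patients per pharmacy**

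Unequal sizes enter through the design effect 1 + ((1 + CV²)m − 1) × ICC. The article gives no CV of cluster size, so the values below are assumed.

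| Pharmacies | CV of size | Power (normal) | Power (t) |
|---|---|---|---|
| 14 | 0 | 80% | 73% |
| 14 | 0.3 | 78% | 70% |
| 14 | 0.5 | 74% | 66% |
| 16 | 0 | 85% | 79.5% |
| 18 | 0 | 89% | 85% |
| 25 | 0 | 96% | 95% |

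The t column uses the number of pharmacies minus 2 as degrees of freedom.

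**The case against.** **The high-risk reading is the natural one.** The calculation opens with the high-risk sample, so 39, 56 and 112 can be read in sequence as high-risk counts. Only the 112 is expressly attached to starters; the sentence giving the 56 says patients. This stands. The defect is one wrong label and one missing conversion, not a wrong calculation.

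**The schedule is already correct.** Fourteen months at 20 starters a month yields 280 invited and 39 analysed, and the 22-month study period described in the same section is built on it. This also stands. A reader might infer that the trial is planned with 63% power. The article does not support that: the figure arises only if recruitment is cut off at the literal numbers, and the target in the stopping rule is nowhere defined as starters of any risk.

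**Fourteen pharmacies is a minimum.** All 25 are to be approached and the Abstract speaks of randomizing 25. With 25, even the literal targets would give more than 80% power. This stands too, although the section bases its calculation on 14 and only consenting pharmacies take part.

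**The 80% is not an arithmetic error.** It reproduces by the standard design-effect method, and the 14 clusters do enter it. A reader might infer that the design cannot reach 80% even at the right count. That holds only near the minimum number of pharmacies and with a t reference. The CVs are assumed, and monitored per-pharmacy targets might limit the spread in size.

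None of this removes the contradiction between 112 starters, 20 starters a month and 14 months, or the absence of a target stated for the population that is actually recruited.

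**Conclusion.** The Sample size section contradicts itself on what the 112 counts. Expressed in starters, the working targets are 140 included and 280 invited per pharmacy, 2.5 times the printed numbers. The planned duration already corresponds to them.

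The consequence is conditional. If inclusion stopped at 56 included or 112 invited starters, power would fall to about 63% (normal) or 56% (t) with 14 pharmacies. With 25 it would be about 87% or 84%. If recruitment runs the full 14 months at the assumed rates, the planned number is reached and nothing is lost. The label still needs correcting, because the stopping rule may rely on it.

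The point about the 80% is secondary. At 14 equal pharmacies it becomes about 73% with t on 12 df, and about 70% to 66% for assumed CVs of 0.3 to 0.5. With 18 or more equal-sized pharmacies power exceeds 80% by the t reference as well.

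These figures rest on the two-sided test, equal allocation and 20-percentage-point effect that reproduce the 39.

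**What to change.** - **Sample size:** label 39, 56 and 112 as high-risk patients. Add the equivalent of about 140 starters included and 280 invited per pharmacy, over 14 months, and correct the sentence that gives 112 starters 14 months.
- **Exclusion criteria:** define the number at which inclusion stops as a count of enrolled patients whose baseline ProMAS is in the high-risk range.
- **Secondary:** state that the 80% at 14 pharmacies assumes a normal reference and equal cluster sizes. Give the power with a t reference for the number of pharmacies actually randomized, with a range for unequal sizes. Naming 16 pharmacies as enough would not settle this: the t-based power is 79.5% with equal sizes, but 77% and 73% at assumed CVs of 0.3 and 0.5.

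The cost is rewording. The duration, assumptions and high-risk sample size stay as they are. Recruitment monitoring has to count high-risk patients, which the baseline questionnaire already identifies. The stated power becomes less favourable if only 14 pharmacies take part.
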